##### Secondary outcome comparison

ED length of stay (in minutes) will be compared between patients who only received the POC whole blood TBI test and those who received the POC whole blood TBI test and a head CT scan using an analysis of covariance model including enrollment site as a covariate. This analysis will be conducted only for participants with a negative POC whole blood TBI test to control for clinical severity of the injury. Differences in these rates following implementation will be evaluated using the same approach (both for the overall cohorts and those with a negative POC whole blood TBI test only). An exploratory receiver operating characteristic AUC analysis will be conducted to differentiate patients who return to the ED for evaluation of the same injury within 2 weeks from those who do not, using whole blood GFAP and UCH-L1 as predictors.

To evaluate the effect of the implementation blueprint on perspectives regarding determinants and implementation outcomes, Mi-PARIHS domain scores will be compared pre- and post-implementation using repeated measures general linear model, including site as a covariate. Secondary comparisons will be made for implementation outcomes (e.g., AIM, FIM, and DCS).

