### Community advisory board

A diverse community advisory board (CAB) of stakeholders related to the implementation of the POC whole blood TBI test in the ED will be assembled to assist in Phases 3 and 4. The CAB will be assembled by the University of Pittsburgh's Clinical Translational Science Institute and will include representatives from each enrolling institution to provide site-specific context. Members of the CAB will include (from each site) recent acute mTBI patients in the ED, hospital administrators, ED physicians, ED staff (e.g., medical assistants), ED nurses, and the team's implementation scientist. The CAB will be assembled two times per year during the study period for a virtual meeting. Objectives of the initial meetings will be to brief the CAB on the final study design, outcomes (and what they mean), and objectives for conducting the study. Input from the CAB will be integrated into study procedures prior to the initiation of the study. Objectives of the subsequent meetings will be to brief the CAB on findings from Phases 1 and 2, and to discuss determinants (in their view) of successful implementation of the test.

#### Phase 1

The goal of Phase 1 is to establish determinants of use for the POC whole blood TBI test for each enrolling site's ED. To accomplish this goal, we will survey ED healthcare providers to identify determinants of routine use, decision-making processes, and perspectives on acceptability, appropriateness, adoption, and fidelity.

To evaluate determinants of routine use, the Mobilizing Implementation of iPARIHS Facilitation Planning tool (Mi-PARIHS) will be administered as the primary outcome measure for this phase. The Mi-PARIHS is a 34-item tool which supports users in their assessment of the innovation, context and recipient constructs, development of a tailored facilitation plan, and repeated use over time to evaluate the effectiveness of facilitation strategies. Each question is rated on a five-item Likert scale to identify barriers and facilitators/enablers for the innovation being evaluated, where −2 indicates a barrier and +2 indicates a facilitator for that aspect of implementation. In alignment with the i-PARIHS framework, domain scores are summed across innovation, recipients, and context items where higher scores indicate more facilitators/enablers and lower scores indicate more barriers.

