The goal of Phase 4 is to test the effect of the implementation blueprint on clinical practice patterns with regard to obtaining head CTs for patients who meet the study's inclusion/exclusion criteria across the three enrolling sites. Approximately 140 patients with presenting GCS scores between 13 and 15 will be enrolled across the three sites. The primary endpoint of Phase 4 (to be compared with the outcome of Phase 2) is the rate of head CTs completed in enrolled patients. The secondary endpoint of this phase is the rate of head CTs completed in enrolled patients with negative POC whole blood test results. We will also evaluate if the implementation blueprint has impacted baseline perceptions of facilitators and barriers and related implementation outcomes (i.e., adoption, appropriateness, acceptability, decisions, and feasibility) has shifted provider's perspectives on the test by having those who completed Phase 1 surveys (e.g., Mi-PARIHS) complete the surveys again.

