### Statistical analysis

Normality will be assessed for all outcomes, and appropriate transformations will be made to ensure that statistical assumptions are met prior to conducting all analyses. Statistical significance for these evaluations will be set at *p* < 0.05, and Bonferroni corrections will be applied to all analyses for multiple comparisons.

#### Phase 1

For Phase 1, descriptive statistics will be calculated for POC whole blood TBI test results, including the rates of elevated vs. non-elevated values, rates of CT scans ordered, and rates of return ED visits for the same injury within 2 weeks in the first group of 140 ED patient participants. Whether or not the patient returned will be self-reported at the 2-week follow-up survey sent to the participants. ED length of stay (in minutes) will be compared between patients who only received the POC whole blood TBI test and those who received the POC whole blood TBI test and a head CT scan using an analysis of covariance model, including enrollment site as a covariate. This analysis will be conducted only for participants with a negative POC whole blood TBI test to control for clinical severity of the injury. An exploratory analysis using receiver operating characteristic area under the curve (AUC) will be conducted to differentiate patients who return to the ED for evaluation of the same injury within 2 weeks from those who do not, using whole blood GFAP and UCH-L1 as predictors. Approximately 5% of patients diagnosed with TBI and GCS scores of 13–15 in the ED return to the ED within 72 h of discharge for TBI evaluation (27). The expected event rate would yield seven returns to the ED for the Phase 2 cohort of *n* = 140, which is lower than the standard expectation of 10 events per predictor. Statistical significance for these evaluations will be set to *p* < 0.05.

#### Phase 2

For Phase 2, descriptive statistics for all determinant measures will be calculated. Items from the Mi-PARIHS will be plotted as originally described for visual inspection of the weakest domains. These statistics will be calculated by site and by stakeholder type to facilitate presentation to the CAB and to inform development of the implementation blueprint.

Phase 3 will not have a corresponding statistical analysis because it is entirely dedicated to the development of the site-specific blueprints.

#### Phase 4

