## Discussion

This study protocol is the first documented hybrid type II effectiveness–implementation study to improve uptake of an objective blood biomarker test for patients with TBI in United States EDs. Our goal is to provide evidence that use of this test can reliably and safely improve clinical practice in EDs by reducing rates of unnecessary radiation exposure, decreasing time spent in the ED, and demonstrating efficacy of an implementation blueprint that can facilitate uptake of this test to meet these goals at similar Level 1 trauma center EDs.

The goals of this study have the potential for significant impact on public health. Researchers have recently suggested, assuming current CT scan trends continue, that cancers associated with repeated CT scans will eventually account for 5% of all new cancer diagnoses annually (28). Reducing CT scan rates for a population where <10% of patients are expected to have intracranial pathology can reduce unnecessary radiation exposure to the millions of mTBI patients evaluated annually in US EDs (1). Reducing length of stay in the ED has obvious benefits for triage efficiency and appropriate allocation of healthcare resources, while also enhancing patient health and wellbeing. A large retrospective cohort study of nearly 200 California hospitals found that patients admitted on high-crowding days experienced 5% greater odds of inpatient death and longer hospital length of stay overall, even after controlling for demographics, clinical complaints, comorbidities, and diagnoses (29). This suggests that prolonged time in the ED environment is associated with higher odds of negative outcomes. Boarding patients in the ED also increases risk for experiencing undesirable events, including missing a relevant medication and preventable adverse events (30). Implementation of the whole blood TBI test offers the opportunity to alleviate some of these concerns. It is important to note, however, that CT utilization rates can be impacted by many factors, including seasonal variation, time of day, changes in institutional policy, and clinician/personnel turnover, all of which could impact study results.

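### The repeated-measures GLM for provider surveys, as usually fitted, drops Phase 1 responders who do not repeat the survey, so the pre/post change risks attrition bias of unknown size and direction

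*Protocol article*

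**What the plan says.** In Phase 1, "we will survey ED healthcare providers to identify determinants of routine use", with the Mi-PARIHS as the primary measure of that phase. The Phase 4 description in the Methods assesses whether the blueprint shifted these views by "having those who completed Phase 1 surveys (e.g., Mi-PARIHS) complete the surveys again". The respondents at the second wave are therefore a closed cohort of Phase 1 responders.

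The analysis stands under Secondary outcome comparison. Its aim is "To evaluate the effect of the implementation blueprint on perspectives regarding determinants and implementation outcomes", and its method is that "Mi-PARIHS domain scores will be compared pre- and post-implementation using repeated measures general linear model, including site as a covariate". Secondary comparisons follow for the other scales, with AIM, FIM and DCS as examples. The article does not give the number of providers, the expected share who repeat the survey, or the treatment of a provider who has only the first survey.

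**The concern.** With two waves, a classical repeated-measures GLM works on the within-provider difference. A provider without a second score has no difference and leaves the analysis, although the baseline score is in the database. The interval between waves is not stated, but it spans at least the development and deployment of the site blueprints. Some responders can be expected to move on or not to answer again.

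If those who do not repeat differ in their views from those who do, the estimated change describes the repeaters and not the group surveyed in Phase 1. At stake is the reading of the provider-level result in a hybrid type II study, where the implementation outcomes are one half of the purpose. The information needed to reduce part of this risk will already have been collected.

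**Working it through.** **The plan's own figures.** The only comparison with a sample size is the CT rate in patients: 95% against 75%, two-sided alpha 0.01, 140 per phase, stated power 0.99. Full enumeration of Fisher's exact test gives power 0.988 at 140 per phase, so that figure reproduces. It does not bear on the provider surveys, for which there is no figure to reproduce.

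**Assumed inputs (none is in the article).** Scores have SD 1 at each wave. The true mean change is 0.3 SD, a value that does not enter the bias formulas below. The pre/post correlation r is 0.3, 0.5 or 0.7. The share m not repeating is 10 to 50%. Loss is either unrelated to scores or follows a logistic model in the baseline score or in the later score, with slope 0.5 or 1.0 per SD, low scorers being lost more often.

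**Formulas.** Let A be the mean of the score that drives loss, among those who repeat, measured from the full-cohort mean in SD.

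- Loss unrelated to scores: A = 0, so the bias of the completers-only change is 0.
- Loss driven by baseline: repeaters start A too high and end r × A too high, so bias = (r - 1) × A.
- Loss driven by the later score: repeaters end A too high and started r × A too high, so bias = (1 - r) × A.

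The simulation (400,000 providers per setting) agrees with these. At m = 50% and slope 1.0, dividing the baseline-driven bias by (r - 1) gives A = 0.293/0.7 = 0.42, 0.205/0.5 = 0.41 and 0.120/0.3 = 0.40 for r = 0.3, 0.5 and 0.7. A is nearly constant, as it should be.

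**Likelihood alternative.** The later score is regressed on baseline in the repeaters and predicted at the baseline mean of all Phase 1 responders. This is what a two-wave mixed model with unstructured covariance does.

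Bias in SD at r = 0.5 and slope 1.0:

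| Not repeating | Loss by baseline: completers | Loss by baseline: mixed model | Loss by later score: completers | Loss by later score: mixed model |
|---|---|---|---|---|
| 10% | -0.044 | 0.000 | +0.046 | +0.069 |
| 30% | -0.126 | -0.002 | +0.127 | +0.196 |
| 50% | -0.205 | +0.003 | +0.207 | +0.325 |

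**Range over all settings.**

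- Loss unrelated to scores: both analyses about 0.
- Loss by baseline: completers -0.02 to -0.29; mixed model about 0.
- Loss by later score: completers +0.01 to +0.29; mixed model +0.03 to +0.38.

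In the last case the mixed model is further off than the completers at every setting tried. It corrects loss that is explained by what was observed, and nothing beyond that.

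**The case against.** The strongest reply is that the article names a model family and does not say that the analysis is limited to providers with both surveys. Rules for missing waves are commonly left to an analysis plan, and none is shown. This stands in part. The absence of a missing-data rule is no fault here. The named model is the fault, because in its usual form it makes the choice by default.

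Four stronger readings are tempting, and the article does not support them.

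- **That the change is biased, and in favour of the blueprint.** Nothing in the article says how many providers will be lost or why. Bias may be zero, negative or positive. A reader might suppose that 60% repeat and change by +5 while the rest would have changed by 0, so that the paired analysis reports +5 against a true 0.6 × 5 + 0.4 × 0 = 3. Those inputs are invented. The example is also loss tied to the unseen later score: with similar baselines a mixed model would report about +5 as well.
- **That leaving out new staff biases the result.** The stated question is whether the views of the providers first surveyed have shifted, and staff without a first score do not bias a within-provider change. Surveying everyone now in post answers a different question, and pooling them would mix staff composition with change in views. What stands is that the result does not represent all staff treating Phase 4 patients.
- **That the authors foresaw survey attrition and ignored it.** The Discussion does list "changes in institutional policy, and clinician/personnel turnover, all of which could impact study results", but that sentence is about CT utilization.
- **That site differences in change are ruled out.** Naming site as a covariate does not show that a site-by-time term is excluded, since the article does not list the model terms.

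Nor are the Phase 1 responses wasted: they serve the descriptive summaries and the building of the blueprint, whatever happens at the second wave.

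**Conclusion.** The point holds as a risk tied to the named method. As conventionally fitted, the repeated-measures GLM discards the baseline of every Phase 1 responder who does not repeat the survey, and the change estimate is then exposed to attrition bias. Under the assumed range the bias is anywhere from zero to about 0.3 SD in either direction. The article gives nothing with which to narrow that range.

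A likelihood-based analysis of all Phase 1 responders removes the part of the bias that depends on baseline views or site, and only that part. The conclusion rests on the usual two-wave behaviour of the model and on some loss occurring. If every Phase 1 responder repeats, or if loss is unrelated to scores, there is no bias. The matter concerns a secondary implementation outcome. The primary comparison of CT rates and the Phase 1 description of determinants are untouched, so this is a worthwhile improvement of low priority.

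**What to change.** Replace the repeated-measures GLM for the Mi-PARIHS domain scores and the other provider scales with a linear mixed model:

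- repeated measures within provider, preferably with unstructured covariance for the two waves;
- fixed effects for time, site and site-by-time, the last because each site has its own blueprint;
- every Phase 1 responder included, whether or not the survey is repeated.

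Keep the paired-completer analysis as a sensitivity analysis, and report by site how many responded at each wave and how many had left. State that the result concerns change among Phase 1 responders. If newly arrived staff are also surveyed, report them separately and do not pool them into the change estimate.

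The mixed model assumes that, given what was observed, non-response does not depend on the later view. Add a sensitivity analysis for failure of that assumption: lower the predicted later scores of non-repeaters by a range of amounts d, so that the overall change becomes the model estimate minus m × d, and report the d at which the conclusion alters. In the invented example above, 5 - 0.4 × 5 = 3.

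The cost is a change in analysis wording and a short table of counts. No extra data are needed unless new staff are surveyed as well.

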## Discussion

This study protocol is the first documented hybrid type II effectiveness–implementation study to improve uptake of an objective blood biomarker test for patients with TBI in United States EDs. Our goal is to provide evidence that use of this test can reliably and safely improve clinical practice in EDs by reducing rates of unnecessary radiation exposure, decreasing time spent in the ED, and demonstrating efficacy of an implementation blueprint that can facilitate uptake of this test to meet these goals at similar Level 1 trauma center EDs.

The goals of this study have the potential for significant impact on public health. Researchers have recently suggested, assuming current CT scan trends continue, that cancers associated with repeated CT scans will eventually account for 5% of all new cancer diagnoses annually (28). Reducing CT scan rates for a population where <10% of patients are expected to have intracranial pathology can reduce unnecessary radiation exposure to the millions of mTBI patients evaluated annually in US EDs (1). Reducing length of stay in the ED has obvious benefits for triage efficiency and appropriate allocation of healthcare resources, while also enhancing patient health and wellbeing. A large retrospective cohort study of nearly 200 California hospitals found that patients admitted on high-crowding days experienced 5% greater odds of inpatient death and longer hospital length of stay overall, even after controlling for demographics, clinical complaints, comorbidities, and diagnoses (29). This suggests that prolonged time in the ED environment is associated with higher odds of negative outcomes. Boarding patients in the ED also increases risk for experiencing undesirable events, including missing a relevant medication and preventable adverse events (30). Implementation of the whole blood TBI test offers the opportunity to alleviate some of these concerns. It is important to note, however, that CT utilization rates can be impacted by many factors, including seasonal variation, time of day, changes in institutional policy, and clinician/personnel turnover, all of which could impact study results.

The literature in this area is sparse due to the relative novelty of using blood biomarkers for TBI assessment. S100B is a protein approved for the same use as the POC whole blood TBI test in Europe. A single-center study evaluated the use of S100B as an adjunct to the Scandinavian Neurotrauma Committee evaluation guideline for patients with minimal, mild, and moderate traumatic head injuries (17). The study found that one in five patient discharges were directly attributable to S100B testing, but compliance with the overall guideline was poor (17). Another study applied these guidelines, including S100B testing, to six emergency departments in the US (18). The authors found that the guidelines worked as intended and their application could have reduced CT usage by one-third. These studies correspond with a growing body of literature suggesting that clinical rules for ordering a head CT are effective but not applied broadly enough in clinical practice (31, 32). These results underscore the need for an implementation science approach, such as the one used in the present study, to actively identify barriers and facilitators to adoption of the POC whole blood TBI test in conjunction with clinical efficacy. One active study aims to compare the rate of head CT utilization between ED physicians blinded to the POC whole blood TBI test results and those who were unblinded to the POC whole blood TBI test results (19). Implementation science is not an explicitly stated method applied in that study's protocol, but the results should provide evidence complimentary to the present study.

### Anticipated impact on clinical practice

Several deliverables will be generated from the completion of this study that can meaningfully impact the clinical practice of evaluating mTBI patients in the ED. The primary deliverable is the open-access publication of site-specific implementation blueprints for designed to increase use of the POC whole blood TBI test. This will allow other Level 1 trauma center EDs with similar patient throughput and demographics to study how the test was implemented, enabling them to tailor strategies to at their own institutional contexts. We will also provide the first known evidence of the clinical utility of the test in predicting return visits to the ED for the same injury within a 2-week period. This protocol will also deliver crucial data on how implementation of the test reduces length of time spent in the ED, which is an endpoint with significant potential to influence uptake from a practical standpoint. Our intent is to use the data generated from the completion of this work to conduct a hybrid type III effectiveness–implementation clinical trial, evaluating the efficacy of optimized interventions to improve clinical uptake of the POC whole blood TBI test in EDs of varying sizes.
